## Abstract

**Objectives::**

to describe an educational intervention using digital technology for family caregivers of older adult stroke survivors to develop caregiving skills.

**Methods::**

randomized pragmatic trial protocol. Fifty-eight family caregivers will be recruited and randomized into two groups. The intervention will consist of a virtual educational action, in addition to telephone contacts at seven, 30, 60 and 80 days after discharge. The control group will not receive the intervention. Primary outcomes will be caregivers’ ability to care, knowledge and performance. Secondary outcomes will be caregiver burden and older adults’ functional capacity. Outcomes will be assessed at the time of participant recruitment and three months after discharge.

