In the local context, there is no evidence that an educational intervention based on skills development can improve caregivers’ ability, knowledge, and performance to provide care to older adults who have survived stroke. Thus, the present study considers the hypotheses that: (1) the educational intervention with digital technology, carried out by nurses for family caregivers of older adults with stroke sequelae, improves caregivers’ ability to care, performance, and knowledge in the intervention group (IG) when compared to caregivers in the control group (CG); (2) the intervention offered reduces caregiver burden; (3) older adults in the IG will present better functional capacity when compared to the CG.

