### Sample size

Sample size was calculated, considering a power of 80%, a significance level of 5% and a Cohen’s effect size of 0.8, adding 10% for possible losses and refusals, totaling 58 participants, divided equally into IG and CG.

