### Statistical methods

For data analysis, the intention-to-treat technique will be used. The difference between baseline and final scores will be assessed by paired Student’s t-test, with a 95% Confidence Interval. A p<0.05 value will be considered significant. For simultaneous intraand intergroup comparisons, the Generalized Estimating Equations model with Bonferroni adjustment will be used.

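### Three primary outcomes but a sample size for one test: depending on the unstated success rule, either the 5% error or the 80% power fails

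*Protocol article*

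**What the plan says.** The abstract of the protocol article lists the primaries: "Primary outcomes will be caregivers’ ability to care, knowledge and performance". The Data collection section gives each its own measure: the ECCIID-AVC for ability to care, and one NOC outcome each for knowledge and performance. Hypothesis 1, at the end of the Introduction, joins them: the intervention "improves caregivers’ ability to care, performance, and knowledge in the intervention group (IG) when compared to caregivers in the control group (CG").

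The Sample size section has one set of inputs, "a power of 80%, a significance level of 5% and a Cohen’s effect size of 0.8", then "adding 10% for possible losses and refusals, totaling 58 participants", "divided equally into IG and CG". It names no outcome and divides no alpha.

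Statistical methods sets the threshold: "A p<0.05 value will be considered significant". It then says that, for comparisons within and between groups, "the Generalized Estimating Equations model with Bonferroni adjustment will be used". The article does not say whether one, some or all of the three primaries must succeed.

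**The concern.** A 5% error rate and 80% power describe one test. With three primary outcomes they describe the trial only once a success rule is fixed, and the two natural rules pull in opposite directions. If any one significant outcome counts, there are three chances of a false positive. If all three must be significant, there are three chances of missing a real effect.

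With the rule open, success could be claimed on whichever outcome falls below 0.05. Alternatively, a trial that works on all three outcomes could fail its joint hypothesis much more often than the stated power suggests.

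**Working it through.** **Inputs from the article.** Three primary outcomes (Abstract); alpha 5%, power 80%, d = 0.8, 10% added, total 58, equal arms (Sample size); threshold p<0.05 (Statistical methods).

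**Assumptions.** The article gives no correlation between the outcomes, so 0 to 0.9 is shown. An effect of d = 0.8 is assumed on every outcome. The test is an unadjusted two-sample t-test with 26 evaluable per arm. Sidedness is not stated; two-sided is used because it reproduces the total.

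**1. Reproduce the 58.** A two-sided two-sample t-test at d = 0.8, alpha 0.05 and power 0.80 (noncentral t) needs 25.5, so 26 per arm and 52 in total. Both 52/0.9 = 57.8 and 52 × 1.10 = 57.2 round up to 58, or 29 per arm. Power at 26 per arm is 80.7%. A one-sided test gives about 20 per arm and does not fit. So 58 is the size for one outcome at the full 5%.

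**2. Any one of three at p<0.05.** Under independence, family-wise error = 1 − 0.95³ = 0.143. Correlated cases were simulated as three equicorrelated normal outcomes.

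**3. All three at p<0.05.** Under independence, joint power = 0.807³ = 0.53. Correlated cases come from the same simulation.

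| Correlation | Any one: family-wise error | Any one: power | All three: power |
|---|---|---|---|
| 0 | 14% | 99% | 53% |
| 0.3 | 14% | 97% | 58% |
| 0.5 | 13% | 95% | 62% |
| 0.7 | 11% | 92% | 67% |
| 0.9 | 8% | 88% | 73% |

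Requiring all three needs no alpha split: the joint claim cannot be falsely made more often than the test of an outcome with no effect, which is 5%. With no effect on any outcome, the simulated error was at most 2.3%. With no losses at all (29 per arm), joint power is about 61% to 78%, still below 80%.

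**4. Alpha controlled across the three outcomes.** Plain Bonferroni uses 0.05/3 = 0.0167 per outcome. Power per outcome is then 66% at 26 per arm and 72% at 29. Holm is never less powerful than this. In simulation at 26 per arm with d = 0.8 on all three, its average per-outcome power is about 73% at correlation 0.7, 74% at 0.5 and 76% at 0.

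**5. Size that would restore 80%.** Per outcome under Bonferroni: 35 evaluable per arm, and 70/0.9 = 77.8, so 78 in total. For all three jointly: about 36 per arm at correlation 0.5 (36/0.9 = 40 per arm, 80 in total) to 38 at correlation 0 (38/0.9 = 42.2, so 43 per arm, 86 in total).

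**The case against.** Four points can be made for the plan.

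- **The Bonferroni sentence might span the outcomes.** The wording is condensed and does not expressly exclude it. If it did, and one success sufficed, family-wise error would be at most 5%. Power for at least one success would be 96% (correlation 0) to 83% (0.7), falling to 76% at 0.9, so both stated figures could hold up to a correlation of about 0.7. However, the sentence attaches the adjustment to comparisons within and between groups, and nothing extends it to outcomes. Nor is one success what hypothesis 1 claims.
- **The GEE on baseline and final scores may be more powerful than the t-test used here.** If d = 0.8 refers to the raw-score SD and the baseline–final correlation is an assumed 0.6 or 0.7, a change-score contrast has d = 0.8/√(2 × 0.4) = 0.89 or 0.8/√(2 × 0.3) = 1.03. Power per outcome is then 89% or 95%, and all-three power under independence is about 69% or 87%. This stands as a limit on the power figures. At a baseline–final correlation of 0.5, or if d is already on the change scale, they are unchanged. The article does not say which scale d refers to.
- **A multiplicity strategy can sit in an analysis plan.** That is true of its detail. But the three primaries, the joint hypothesis and the one-test size are fixed here. A later plan could control the error, but it could not by itself make the stated 80% apply to the joint hypothesis.
- **The Sample size section never claims 80% for the joint hypothesis.** That is also true; it ties the figure to no outcome, which is the gap.

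A reader might infer that the 5% and the 80% both fail. The document does not support that. Under the any-one rule only the error fails, and under the all-three rule only the power falls short. Nor is 58 miscalculated: it is right for one outcome.

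**Conclusion.** The point holds in a limited form: the sample size supports 5% error and 80% power for one primary outcome, while the article has three and no success rule. As the text stands, one of the two figures fails, and which one depends on the rule. Family-wise error is about 8–14% if any one outcome suffices. Joint power is about 53–73% if all three are required, which is how hypothesis 1 reads.

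The error range rests on the assumed correlations and on taking the Bonferroni sentence at its natural scope. The power range also rests on d = 0.8 for every outcome, 26 evaluable per arm and an unadjusted t-test, and could be better under a GEE that gains from baseline.

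**What to change.** Before outcome data are seen, choose one of two routes.

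1. **One primary outcome.** Name it and test it at two-sided 5%. Test the other two in fixed sequence, each at 5% only if the preceding test succeeds, and state in Sample size that the 80% applies to the named outcome only. The ECCIID-AVC is one reasonable choice: the Introduction says the predecessor study did not assess caregivers' ability, and the Discussion stresses the scale's first use. The other two (NOC) outcomes would then follow in a stated order.
2. **Keep all three.** State the success rule and the scope of the Bonferroni adjustment, and restate the power.
   - If any one suffices, apply Holm across the three outcomes. Per-outcome power is then at least 66% (the plain Bonferroni floor at 26 per arm) and averages about 73–76% at correlations 0.7 to 0 if all three effects are 0.8.
   - If all three are required, keep 5% for each and state the joint power of about 53–73% with its assumptions.

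Neither route needs more participants unless 80% is to be restored under three primaries, which would take about 78 to 86 in total. The cost is that two outcomes become only conditionally confirmatory, or that the stated power is less favourable. The Study location section describes the study as under way, so any change to the published primaries must be dated, justified and documented.

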### Eligibility criteria

Study participants are family caregivers of older adults selected at hospital admission who play the role of primary care provider. Family caregivers of older adults will be excluded from the study if: (a) they live in a long-term care facility; (b) they do not have access to the internet and a device to access it, or are not able to use them, as verified through a digital aptitude checklist developed for the study; (c) they do not have a telephone line for contact; (d) they are accompanying older adults who died during the participant recruitment phase.

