**Figure 1 f1:**
[figure not shown]
Graphical representation of study logistics diagram and operationalization of data collection, Porto Alegre, Rio Grande do Sul, Brazil, 2024

The study will begin with the identification of patients aged 60 or older who have a medical diagnosis of stroke during their current hospitalization. The older adults selected will receive a visit from the researchers to verify the existence of a family caregiver and to assess whether the caregiver and the older adult meet the inclusion criteria. Baseline data will be collected for those who agree to participate. After allocation, those included in the IG will receive an instructional visit from the intervention nurses close to discharge. The purpose of the visit is to provide detailed guidance on the intervention.

Caregivers will be contacted by telephone three months after discharge to conduct the final assessment. Data collection will be done via online conference. The three-month interval meets Brazilian reproducibility study of the Scale of Informal Caregiver Capabilities for Older Adults Dependent on Stroke (ECCIID-AVC) recommendations, which will be used in the study^(7)^.

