### Allocation

After the instruments are applied, participants will be randomized to either the CG or IG group. To do this, a list generated by the website randomizer.org will be used. A professional external to the research group will be responsible for the list.

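### For burden and direct-care performance, change from the in-hospital baseline mixes the move to home care with the intervention effect, and the plan does not make the between-arm contrast the deciding test

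*Protocol article*

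**What the plan says.** **Timing.** The abstract sets two assessments: "Outcomes will be assessed at the time of participant recruitment and three months after discharge". Eligibility criteria reads: "Study participants are family caregivers of older adults selected at hospital admission who play the role of primary care provider". Under Participant timeline, the study starts with "identification of patients aged 60 or older who have a medical diagnosis of stroke during their current hospitalization". A recruitment visit follows, and then: "Baseline data will be collected for those who agree to participate". The Allocation section puts the measurements before randomization: "After the instruments are applied, participants will be randomized to either the CG or IG group". The instructional visit to the intervention group comes later, near discharge.

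**Instruments.** Data collection applies every instrument at both time points. These include the CBS (burden, a secondary outcome) and the Nursing Outcomes Classification outcome Caregiver Performance: Direct Care (performance is among the primary outcomes). No separate baseline or reference period is given for either.

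**Hypotheses (Introduction).** Hypotheses 1 and 3 name the control group. Hypothesis 2 says only that "the intervention offered reduces caregiver burden".

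**Analysis (Statistical methods).** "The difference between baseline and final scores will be assessed by paired Student’s t-test", with significance at p<0.05. The same paragraph plans a GEE model with Bonferroni adjustment for comparisons within and between groups.

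**The concern.** The protocol places the care it wants to improve after discharge: its Introduction says survivors go home and depend on the caregiver there, and the intervention prepares caregivers for that period. The baseline burden and direct-care scores are taken before that period starts. A relative who becomes a caregiver because of this stroke has given no home care after it. A relative who was already caring can only rate care before the stroke or in hospital. In both cases the three-month score describes a different situation from the baseline score.

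A paired test takes two scores from the same people and contains no comparison between arms. It therefore picks up whatever the transition to home does to the score, together with any effect of the course. Two misreadings are possible:

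- Direct-care performance may appear to improve in both arms because home care has begun.
- Burden may rise in the intervention arm although it rises less than in the control arm, and the intervention would then be reported as not reducing burden.

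Hypothesis 2 invites the second misreading because it speaks of a reduction and names no comparator.

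**Working it through.** **1. The plan's own sample size.** Inputs from Sample size: power 80%, significance level 5% (two-sided assumed), Cohen's d 0.8, 10% added for losses and refusals. The two-sample t-test needs 25.5, so 26 per arm and 52 in total. 52/0.9 = 57.8 and 52 × 1.1 = 57.2; both round up to 58. The stated 58 is reproduced and is not in dispute. It rests on a between-arm effect size, and 26 completers per arm are used below.

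**2. What the paired test picks up with no intervention effect.** Assume a common shift s (in SD units) from the hospital baseline to three months at home, equal SDs at both times, and baseline-final correlation r. The SD of the change is √(2(1 − r)), so the paired test has standardized effect s/√(2(1 − r)). Probability of p<0.05 in one arm of 26:

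| Shift s | r = 0.2 | r = 0.5 | r = 0.8 |
|---|---|---|---|
| 0.3 SD | 0.214 | 0.313 | 0.642 |
| 0.5 SD | 0.491 | 0.688 | 0.972 |
| 0.8 SD | 0.873 | 0.975 | 1.000 |

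All values of s and r are assumptions, because the documents give neither.

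**3. What the between-arm comparison picks up.** In 20,000 simulated trials with s = 0.5 SD, 26 per arm and no intervention effect, the comparison of change between arms was significant in 4.985% (r = 0.2) and 4.975% (r = 0.5). The mean between-arm difference was −0.0002 and 0.001 SD. The shift cancels because baseline precedes randomization.

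**4. How the two readings can disagree.** Suppose burden rises 0.8 SD in the control arm and 0.3 SD in the intervention arm (both values assumed). The between-arm contrast is 0.3 − 0.8 = −0.5 SD, a benefit. The within-arm change in the intervention group is +0.3 SD, an increase in burden.

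**5. Which between-arm contrast is most precise.** Relative outcome variances are 1 for the final score, 2(1 − r) for change, and 1 − r² for the final score adjusted for baseline. Number per arm for 80% power at 0.8 SD (two-sample t-test with these variances):

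| r | Final score | Change | Baseline-adjusted |
|---|---|---|---|
| 0.2 | 26 | 41 | 25 |
| 0.5 | 26 | 26 | 20 |
| 0.8 | 26 | 11 | 10 |

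The adjusted contrast needs the fewest in every row. If the hospital and home scores correlate weakly, change scores cost the most: 41 per arm, against 26 on the final score.

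**The case against.** The strongest reply is that the plan already contains the right analysis. The GEE model covers comparisons between groups, and in the example above its between-arm contrast would return the correct −0.5 SD. Nothing names the paired test as the test of hypothesis 2. In a randomized trial with a control arm, a claim of reduced burden is naturally read as relative to control. On this view the point is the general caution against within-group tests, and the remedy is an edit.

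Much of this stands. The between-arm contrast is unbiased, and the trial can answer its question. What remains is that the paragraph lists the paired test first, states a significance threshold, and does not say which analysis decides. Hypothesis 2 is also the only one of the three without a comparator.

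A reader might infer three stronger points, which the documents do not support:

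- **That the baseline scores have no content.** Eligibility criteria describes participants as already in the primary caregiving role, and the share of new caregivers is not given. The CBS items and recall period are not reproduced. Data collection says that operational definitions were built for each nursing-outcome indicator, but they are not shown.
- **That burden is bound to rise in both arms.** This is plausible, but no figure or statement in the documents establishes it.
- **That the baseline score should be discarded, for example in favour of a yes/no item on earlier caregiving.** A score taken before randomization is a valid covariate even if it measures something different from the final score. At r of 0.2 to 0.5 it removes r², or 4% to 25%, of the outcome variance.

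**Conclusion.** The point holds for within-arm change only. For burden and direct-care performance, a significant paired test would not separate the intervention from the move to home care, and it cannot support hypothesis 2 as worded. With no intervention effect, the paired test would be significant in 21% to 100% of trials over the assumed range, while the between-arm comparison of change stays at 5% where it was simulated. Any non-zero common shift raises the paired test's rate above 5%; how far depends on shifts and correlations that the documents do not give. The precision comparison likewise depends on the assumed correlation.

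The defect lies in which test is allowed to decide. The design and the sample size of 58 are unaffected, and the randomized contrast is already within reach of the planned model. It is worth correcting because the change is cheap and affects one of the primary outcomes and one secondary outcome.

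**What to change.** 1. Reword hypothesis 2: caregiver burden at three months is lower in the IG than in the CG.
2. In Statistical methods, for CBS and Caregiver Performance: Direct Care, make the between-arm difference at three months, adjusted for the baseline score, the test of effect. The planned GEE framework can be specified to give it.
3. State that the paired within-arm tests are descriptive and are not evidence of effect.
4. Optionally, add a yes/no covariate for whether the caregiver already cared for this person before the stroke, alongside the baseline score and not in its place. The article does not list the questionnaire's items, so this may already be recorded; if not, it is one more item.

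**Cost.** The wording of one hypothesis and of the analysis paragraph, with at most one questionnaire item. No extra visits or participants are needed. The downside is that within-arm p-values for these two outcomes no longer count as evidence that the intervention works.

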**Results::**

this research aims to provide support that demonstrates the effectiveness of virtual interventions as a means of education and development of care skills.

**Conclusions::**

it is expected that the intervention will contribute to training caregivers and reducing their burden.

## INTRODUCTION

The proportion of individuals diagnosed with stroke increases with age, being more prevalent in older adults. In Brazil, in 2022, stroke accounted for 35,982 deaths, 88% of which were in individuals aged 60 or over^(1)^.

After discharge, stroke survivors often return home, where they rely on emotional and physical support from caregivers. In most cases, these family caregivers do not have the knowledge, training, or resources to provide the necessary care^(2)^. In Brazil, there are currently no structured support programs for family caregivers, and there is a gap in national health policies aimed at home care^(3)^.

In southern Brazil, the Nursing Home Care Intervention Post Stroke (SHARE) study offered an educational intervention to family caregivers of older adults after stroke through home visits within one month after hospital discharge. The intervention consisted of preparing caregivers to perform activities of daily living (ADLs) for older adults, providing emotional support, and providing guidance on using healthcare services. The results showed a low impact of the intervention on the outcomes of interest. The study did not assess caregivers’ ability to provide care, so the authors suggested that research be conducted to assess caregivers’ ability^(3)^.

In the international scenario, a cross-sectional study conducted in Malaysia aimed to determine the level of knowledge among caregivers and their level of confidence in caring for patients after a stroke. The findings reinforce the need for training programs for caregivers and policies that ensure their implementation in healthcare services^(2)^.

Recently, due to the COVID-19 pandemic, many healthcare and research activities have been suspended or altered. During this period, greater vulnerability was identified in older adults as the age group with the highest risk of death, especially those with comorbidities, such as stroke. To meet this demand, healthcare and research strategies in virtual environments have been intensified^(4)^.

In the local context, there is no evidence that an educational intervention based on skills development can improve caregivers’ ability, knowledge, and performance to provide care to older adults who have survived stroke. Thus, the present study considers the hypotheses that: (1) the educational intervention with digital technology, carried out by nurses for family caregivers of older adults with stroke sequelae, improves caregivers’ ability to care, performance, and knowledge in the intervention group (IG) when compared to caregivers in the control group (CG); (2) the intervention offered reduces caregiver burden; (3) older adults in the IG will present better functional capacity when compared to the CG.

